### Sample size {14}

We calculated the sample size needed for comparison of means between selected arms as detailed in the trial design. This was done independently for the primary and secondary outcomes based on the score of each questionnaire scale, upon which we selected the most conservative sample size for our study.

The sodium questionnaire consists of 8 questions, each comprising a different number of items. In total, the participants can score up to 30 points by correctly answering all of the items in the questions. As this is a new questionnaire, there is no prior information on the average score and its variability in the general population; thus, the effect size cannot be directly estimated. In addition, we assume that a consistent change in knowledge through watching an animated video could be achieved by watching the video not only once, but several times. As our study provides a one-time view of the video and measures the effect afterwards, we aim to measure a small change in the average score, presuming that these small changes could turn into larger ones by watching the video again. Thus, we power the trial to detect a small effect size for comparing the mean score between samples, i.e., *d*=0.1, smaller than the generally recommended threshold for detecting a small effect size [11]. We used the sample size formula for one-tailed comparison of the mean score with equal variance, a type I error of 0.01 to account for multiple comparisons, and a power of 80% to detect the changes in the mean score. This resulted in a sample size of 2009 individuals per arm. Accounting for a potential attrition rate of 20% (personal communication with ProA), this yields 2410 individuals per arm. For this study, we will recruit 10,000 participants (2500 per arm), which allows us to detect the potential changes in the intervention with a power higher than 80%.

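### The 20% attrition allowance is multiplied on (2410 per arm) instead of divided out (2512), so the power claim narrowly fails at week 2

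*Protocol article*

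**What the plan says.** All the inputs stand in the protocol article under Sample size {14}. The target is a standardised mean difference of 0.1. The method is described as follows: "We used the sample size formula for one-tailed comparison of the mean score with equal variance", with "a type I error of 0.01 to account for multiple comparisons" and "a power of 80% to detect the changes in the mean score". The result is given as: "This resulted in a sample size of 2009 individuals per arm". The allowance for loss follows: "Accounting for a potential attrition rate of 20% (personal communication with ProA), this yields 2410 individuals per arm". The section then rounds up to 2500 per arm (10,000 in total), "which allows us to detect the potential changes in the intervention with a power higher than 80" per cent.

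Two other sections decide where the loss falls. Outcomes {12} makes both the immediate and the medium-term effect on knowledge primary. The section on non-adherence and missing data {20c} keeps a participant who completes time point 1 but not time point 2 in the immediate analysis only. Attrition between the two rounds therefore reduces the week-2 comparison and leaves the immediate one intact.

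**The concern.** An attrition allowance should leave the required number of completers once the assumed share has dropped out. Adding 20% to the required number does not do this, because the 20% loss then applies to the enlarged number. An allowance of × 1.2 covers a loss of only 1 − 1/1.2 = 16.7%.

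Two statements depend on the step. The first is the figure of 2410 itself, which a reader would take as the recruitment needed. The second is the claim that 2500 per arm gives more than 80% power. Against 2410, recruiting 2500 looks like a reserve of 90 per arm. Against the correct requirement there is no reserve. The comparison affected is a primary outcome, and one power statement currently covers two time points whose analysed numbers differ.

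**Working it through.** **Inputs (all from Sample size {14}):** d = 0.1 with SD = 1; one-tailed α = 0.01; power 80%; attrition 20%; 2500 recruited per arm. Normal quantiles: z(0.99) = 2.3263 and z(0.80) = 0.8416.

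**Step 1. Reproduce the plan's 2009.**

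n = 2 (z(0.99) + z(0.80))² / d² = 2 × (3.1680)² / 0.01 = 2007.2, so 2008 per arm by the normal approximation. The noncentral t calculation gives exactly 2009. The plan's figure reproduces.

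**Step 2. Reproduce the 2410.**

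2009 × 1.2 = 2410.8, which is the printed 2410 when truncated.

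**Step 3. Apply the allowance correctly.**

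2009 / (1 − 0.20) = 2511.25, so 2512 per arm, or 4 × 2512 = 10,048 in total. The printed figure is 102 per arm too low (102 / 2410 = 4.2%), which is more than rounding.

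**Step 4. Compare with the number actually recruited.**

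- Recruits: 2512 − 2500 = 12 per arm short (0.5%).
- Completers at 20% loss: 2500 × 0.8 = 2000, which is 2009 − 2000 = 9 per arm short.
- Largest loss that still leaves 2009: 1 − 2009/2500 = 19.6%.

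**Step 5. Power at each number.**

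Normal approximation: power = Φ(d √(n/2) − z(0.99)).

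- n = 2000: 0.1 × √1000 = 3.1623; Φ(3.1623 − 2.3263) = Φ(0.8359) = 0.798.
- n = 2500: 0.1 × √1250 = 3.5355; Φ(3.5355 − 2.3263) = Φ(1.2092) = 0.887.

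| Situation | Analysed per arm | Power, normal | Power, noncentral t |
|---|---|---|---|
| Time point 1, all recruits analysed | 2500 | 88.7% | 88.7% |
| Plan's target number of completers | 2009 | 80.0% | 80.0% |
| Week 2, 20% lost from 2500 | 2000 | 79.8% | 79.8% |
| Week 2, had only 2410 been recruited | 1928 | 78.2% | 78.2% |

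The last row shows what the printed 2410 would deliver (2410 × 0.8 = 1928). It does not describe the planned trial.

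**The case against.** The best case for leaving the text alone is that 2410 is only an intermediate figure. The trial recruits 2500 per arm, and rounding up removes nearly all of the error. At exactly 20% loss the claim misses by 0.2 percentage points; at any loss below 19.6% it holds. The protocol calls 20% only a potential rate, pays participants only after the follow-up questionnaire ({15, 11c, 18b}), and expects little loss to follow-up (Discussion). The planned covariate-adjusted regression could also recover 9 completers per arm if the covariates explained about 0.5% of the score variance (1 − 2000/2009 = 0.45%).

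Most of this stands, and it settles the severity: the design is not materially underpowered. It does not make 2410 correct. Nor does it rescue the power claim on the plan's own inputs, since 20% is the rate the plan chose to allow for and the t-test is what it was sized on.

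A reader might infer more in three ways.

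- **That the slip calls for more recruitment.** A gap of 12 recruits per arm and 0.2 points of power does not justify that.
- **That week-2 power is really about 72%.** That is the figure for a two-sided test at 0.01 with 2000 per arm. It does not come from the attrition step: 2009 completers would give only about 72.3% two-sided. Nor does the protocol say that the tests are two-sided. The calculation is explicitly one-tailed, Objectives {7} states a direction for knowledge, and the analysis section {20a} names the t-test without giving its sidedness. That detail is commonly left to an analysis plan, which is not shown here.
- **That a different α, such as a two-sided 0.025, should be adopted.** Nothing in the protocol supports it. The protocol's own allowance for multiple comparisons is the 0.01.

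**Conclusion.** Wrong as written, with a small effect. The correct inflated number is 2512 per arm; 2410 understates it by 102. With 2500 recruited and the assumed 20% lost, week-2 power is 79.8%, so the claim of more than 80% is not met for the medium-term primary outcome. It is met for the immediate outcome, at about 89%.

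These figures rest on the plan's own d = 0.1, equal variances, one-tailed α of 0.01 and a loss of exactly 20% in each arm compared. The 89% also assumes that every recruit in the arms compared is analysed at time point 1. Exclusions under {20c} for not watching the video or not answering would lower it somewhat.

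**What to change.** In Sample size {14}:

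1. Replace 2410 with 2512 and show the step as 2009 / 0.8.
2. Replace the single claim of power above 80% with power by time point, at d = 0.1 and a one-tailed 0.01: about 89% for the immediate comparison with 2500 per arm, and just under 80% (79.8%) for the week-2 comparison with 2000 per arm after 20% attrition.

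Keep recruitment at 2500 per arm. The cost is two sentences of text. No test, arm or enrolment target changes, and the stated week-2 power becomes slightly less favourable.

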### Recruitment and strategies to improve adherence to interventions, promote participant retention, and complete follow-up {15, 11c, 18b}

Adequate participant enrolment to reach the target sample size will be guaranteed by Prolific Acedemic (ProA). ProA has a sufficiently large database of registered prospective trial participants.

The major strategy to improve adherence to the interventions in this trial is to offer payment to all participants. The payments will be given only after completing the whole survey (i.e., once the medium-term follow-up questionnaire is finished). If participants spend more than 45 min on any phase of the trial, they will be timed out of the experiment. This prevents participants from burdening the system with partially completed questionnaires. Throughout the study, investigators will have no access to the identity of the participants, so follow-up with individual participants is not possible. All incomplete datasets from participants who discontinue or deviate from intervention protocols will be descriptively reported.

### Sequence generation, allocation concealment, and implementation: {16a, 16b, 16c}

This 4-arm randomized controlled online study will be hosted and implemented by the *Gorilla experiment-builder platform*. The platform will use a computer-generated allocation sequence to randomly allocate participants 1:1:1:1 to the four trial arms. There is no human involvement, and the process is fully concealed from both study investigators and prospective participants until the study arm is assigned. The investigators will remain unaware of individual trial arm allocations.

### Blinding {17a and 17b}

All study investigators and researchers involved in the data analyses will remain blinded to the trial arm allocation for the entire study duration. Unblinding will not be required.

### Participant timeline: {13}

Participants will be enrolled over a 4-week period on the Prolific Academic platform. Phase 1 of the trial (video viewing and subsequent knowledge testing) will occur on a rolling basis, with Phase 2 (follow-up knowledge testing) taking place 2 weeks subsequently, across all arms. After both phases have been completed, each participant will be offered post-trial access to both videos. Their voluntary view time will be recorded as a measure of participant engagement with this health education medium (Table 1).

**Table 1 Tab1:** Schedule of enrolment, interventions, and assessments

**Timepoint****	**Study period**							
	**Enrolment**	**Allocation**	**Post-allocation**					**Close-out**
	***-t***_***1***_	**0**	***Intervention video (t***_***1***_***)***	***Attention placebo video (t***_***1***_***)***	***Sodium and behavioral expectation questionnaire (t***_***1***_***)***	***2-week interval***	***Sodium and behavioral expectation questionnaire (t***_***2***_***)***	***Post-trial video access (all videos)***
**Enrolment:**								
**Eligibility screen**	X							
**Informed consent**	X							
**Allocation**		X						
**Interventions and assessments:**								
***Intervention Arm***			X		X	X	X	X
***Do-nothing Exposed Arm***					X	X	X	X
***Attention Placebo Arm***				X	X	X	X	X
***Do-nothing Un-exposed Arm***						X	X	X

### Relevant concomitant care permitted or prohibited during the trial {11d}

There are no restrictions regarding concomitant care during the trial.

### Criteria for discontinuing or modifying allocated interventions {11b}

Participants may withdraw their consent to participate in the study at any time before or during the study. Data from incomplete surveys will not be used in the primary analysis, except at a meta-level to report the aggregate number of incomplete surveys.

### Provisions for post-trial care {30}

During this trial short, animated storytelling videos will be displayed and questions related to the health effects of sodium intake and behavioral expectations regarding sodium consumption will be asked. The trial will be conducted purely online.

There are no foreseeable risks associated with participating in this study. Participants volunteer and consent to participate in the study and can withdraw at any time. The authors of the study can be contacted at any time after the study, should the participants wish to follow up.

### Plans for assessment and collection of outcomes: {18a}

The Gorilla platform will collect data submitted by individual participants as they select their responses to the knowledge and behavioral expectations questions. We anticipate completing all data collection within a 4-week window.

### Data management {19}

Gorilla will store all data on their secure cloud platform, hosted on Microsoft Azure in the Republic of Ireland. Encryption of the Gorilla database is ensured by industry-standard cryptography, however, the research team controls and maintains ownership of all data. The research team can access only anonymized data sets and, for statistical analysis purposes, we will download and safely store this data on secure computers maintained by our co-investigators at Heidelberg University, Germany.

### Statistical methods for analyzing primary and secondary outcomes {20a}

#### Descriptive statistics

Descriptive statistics will be used to summarize the distribution of the measured scores by demographic factors, including factors such as gender, age, region, political affiliation, socio-economic status, ethnic, and minority, since these factors could affect the scoring.

#### Primary outcomes

For each participant, the overall score achieved in the sodium questionnaire will be calculated individually. The mean score for each study arm at time point 1 and time point 2 (i.e., re-assessment 14 days after entering the trial) will be calculated and compared between the *Intervention Arm*, the *Attention Placebo Arm*, and the *Do-nothing Exposed Arm* at time point 1 and between all four study groups at time point 2, using the *t*-test for two independent groups. We will also use multilevel regression analyses to control for demographic factors and other potential variables as needed. The analyses will be conducted using the R statistical software package (R 4.2.2).

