#### Secondary outcomes

For evaluation of secondary outcomes, we will use the statistical methods described above to evaluate both the immediate and medium-term effects of the SAS video intervention on behavioral expectations to reduce sodium intake. The methods include, but are not limited to, *t*-test for independent groups, matched t-test for dependent groups, and multilevel regression model. For that, we will analyze the mean scores of the Sodium questionnaire at time points 0 and after 14 days, with a focus on the impact of the SAS video intervention (“Intervention Arm”) on the score outcomes. We will use the program R 4.2.2 for the statistical analyses.

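### The primary knowledge comparison pairs an unadjusted t-test with an open-ended adjusted regression and does not rank them; one fixed adjusted model would be at least as precise and would settle which estimate is primary

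*Protocol article*

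**What the plan says.** In the protocol article, under Statistical methods {20a}, Primary outcomes, the mean knowledge score is compared between three arms at time point 1 and four arms at time point 2, "using the *t*-test for two independent groups". The next sentence adds a second analysis of the same outcome: "We will also use multilevel regression analyses to control for demographic factors and other potential variables as needed". The section does not say which result is primary.

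Under Descriptive statistics, scores are to be summarised by demographic factors, "including factors such as gender, age, region, political affiliation, socio-economic status, ethnic, and minority, since these factors could affect the scoring". The list is introduced as examples, so it is not closed.

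Under Sample size {14}, the trial is sized on a one-tailed comparison of two means with d = 0.1, type I error 0.01 and 80% power. This gives 2009 per arm, with 2500 per arm to be recruited. No covariate enters the calculation. On the new questionnaire, the section says that "there is no prior information on the average score and its variability in the general population".

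Table 1 shows no knowledge questionnaire before the video in any arm, so there is no pre-test score to adjust for.

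**The concern.** The plan itself says that demographics may influence the score, yet the analysis named first, and used for sizing, ignores them. Without a pre-test, they are the only prognostic variables that the plan names. The time point 1 score cannot stand in at time point 2: it is measured after randomisation, and the unexposed control arm does not have it.

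Two things are at stake. The first is precision: a primary analysis adjusted for prognostic variables has a smaller standard error for the same number of participants. The second is pre-specification: with two unranked analyses and an open covariate set, a reader of the results could not tell from this text which estimate was meant to carry the primary conclusion.

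**Working it through.** **Inputs.** From Sample size {14}: d = 0.1 (SD set to 1), one-sided alpha 0.01, power 80%, attrition 20%, 2500 recruited per arm. R² is **assumed**, because the document gives neither R² nor the SD of the score.

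**Step 1: reproduce the plan's figure.** The normal approximation is n = 2(z₀.₉₉ + z₀.₈₀)²/d² = 2(2.326 + 0.842)²/0.01, which gives 2008 per arm. The t-based solution is 2008.56, rounded up to the stated 2009. A two-sided test at 0.01 would need 2336. The stated figure is therefore that of an unadjusted, one-sided, two-sample comparison.

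**Step 2: unadjusted power.** Power = Φ(d/√(2/n) − 2.326).
- n = 2500 × 0.8 = 2000: Φ(3.162 − 2.326) = 79.8%.
- n = 2500: Φ(3.536 − 2.326) = 88.7%.

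**Step 3: power after adjustment.** Covariates that explain a share R² of the score variance reduce the residual SD to √(1 − R²). Power becomes Φ(d/[√(1 − R²)·√(2/n)] − 2.326), and the equivalent sample gain is 1/(1 − R²) − 1.

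| Assumed R² | Reduction in SE | Equivalent sample gain | Power, 2000 per arm | Power, 2500 per arm |
|---|---|---|---|---|
| 0 | 0% | 0% | 79.8% | 88.7% |
| 0.02 | 1.0% | 2% | 80.7% | 89.3% |
| 0.05 | 2.5% | 5% | 82.1% | 90.3% |
| 0.10 | 5.1% | 11% | 84.3% | 91.9% |
| 0.15 | 7.8% | 18% | 86.5% | 93.4% |

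**Step 4: a bound on the cost of leaving the analyses unranked.** Suppose, hypothetically, that the more favourable of the two tests were reported. Under the null hypothesis the two statistics have correlation of about √(1 − R²), and the one-sided error is 1 − P(Z₁ ≤ 2.326, Z₂ ≤ 2.326). This gives 0.0115 at R² = 0.02, 0.0124 at 0.05, 0.0133 at 0.10 and 0.0141 at 0.15, against a nominal 0.010 per contrast. Freedom in the choice of covariates is not counted.

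**The case against.** The strongest reply is that the t-test is the primary analysis in all but name. It is stated first, the regression is introduced as an addition, and the trial is sized on it. Under 1:1:1:1 randomisation it is valid. An adjusted estimate is also planned, and the qualifier 'as needed' may attach only to the other potential variables, so that demographic adjustment would happen in any case. Covariate lists are commonly left to an analysis plan, which is not shown. All of this stands. It means that the ambiguity is partial and that no bias follows.

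Three stronger readings are tempting, and the document does not support them.
- *The plan throws precision away.* It does not, because a regression with demographics is planned. The adjusted result is simply not designated as primary.
- *The plan produces two primary answers, and the investigators will choose after seeing the data.* The text does not provide for such a choice. Blinding {17a and 17b} keeps the researchers who analyse the data unaware of arm allocation, which limits result-driven selection. The error rates in Step 4 are therefore conditional and do not describe what the plan will do.
- *The open wording under Secondary outcomes ("The methods include, but are not limited to") shows that the primary analysis is equally open.* That sentence concerns behavioural expectation, not the primary outcome.

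The size of the gain is also uncertain. At R² = 0.02 it is under one percentage point of power. If attrition falls only between the two visits, time point 1 has about 2500 per arm and 88.7% power without adjustment, so precision matters mainly at time point 2. The small shortfall there (79.8% against 80%) comes from the attrition arithmetic: 2009 × 1.2 gives about 2410, whereas 2009/0.8 gives 2512. That is a separate matter.

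The reply does not remove two facts: the two analyses are unranked, and a better primary estimate is available from variables that the plan already intends to use.

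**Conclusion.** The point holds as one of efficiency and pre-specification. The protocol article leaves the adjusted regression beside the t-test with an open covariate set and no statement of which is primary, although it lists demographics "since these factors could affect the scoring". The t-test is valid and is the likely default.

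For assumed R² of 0.02 to 0.15, making the adjusted model primary adds about 1 to 7 percentage points of power with 2000 completers per arm, and about 1 to 5 points with 2500 per arm. These figures rest on the plan's d, alpha and attrition and on an R² that the document does not supply. Only if the more favourable test were reported would the one-sided error per contrast rise from 0.010 to about 0.0115 to 0.014, and the text does not say that this would be done.

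**What to change.** At each time point, define the primary estimate as the arm difference from one linear regression of the knowledge score on arm plus a fixed list of demographics, with robust standard errors. Choose the list from those under Descriptive statistics, for example age, gender, region, socio-economic status and ethnicity. State that each variable is recorded before randomisation, since Table 1 does not show when demographics are collected. Each participant has one score per time point, so an ordinary linear model is enough for these comparisons.

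Report the t-test as supportive. For the primary analysis, delete 'as needed' and 'other potential variables'; any wider adjustment can be labelled exploratory. If the investigators prefer to keep the t-test as primary, saying so explicitly would settle the ranking but would forgo the precision.

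The cost is a few sentences in the protocol or analysis plan and one regression per time point. No extra participants are needed, and no data beyond the demographics already planned for the descriptive summaries.

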#### Secondary outcomes

For evaluation of secondary outcomes, we will use the statistical methods described above to evaluate both the immediate and medium-term effects of the SAS video intervention on behavioral expectations to reduce sodium intake. The methods include, but are not limited to, *t*-test for independent groups, matched t-test for dependent groups, and multilevel regression model. For that, we will analyze the mean scores of the Sodium questionnaire at time points 0 and after 14 days, with a focus on the impact of the SAS video intervention (“Intervention Arm”) on the score outcomes. We will use the program R 4.2.2 for the statistical analyses.

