### Objectives {7}

In this study, we aim toEvaluate the effect of SAS videos on knowledge about dietary sodium intake in the short- and medium-termEvaluate the effect of SAS videos on behavioral expectation to reduce sodium consumption in the short- and medium-termMeasure voluntary engagement with SAS video content

We hypothesize, that SAS videos help increase knowledge about dietary sodium intake in the short- and medium-term, but knowledge may decrease during the 2-week follow-up phase.

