## Methods

### Trial design {8}

This study is a randomized-controlled parallel-group trial examining the effect of a short, animated storytelling video on knowledge and behavioral expectation to reduce dietary sodium intake. We will use an online academic research platform (Prolific Academic) to recruit and randomize 10,000 participants aged 18–59 years into four study groups.

In group 1 (intervention group), participants will be shown a SAS video on dietary sodium (see multimedia Appendix) and thereafter be asked to complete a questionnaire to assess knowledge on dietary sodium and behavioral expectation.

In group 2 (exposed control group), participants will be asked to complete a questionnaire to assess knowledge on dietary sodium and behavioral expectation (the same questionnaire as in group 1), however, without being exposed to the SAS video on dietary sodium before.

In group 3 (attention placebo control group), participants will be shown an attention placebo control (APC) video, unrelated to the outcomes measured in this trial, before being asked to complete the knowledge and behavioral expectation questionnaire.

Participants in group 4 (unexposed control group) will not view a video and will not be asked to complete the questionnaire.

Two weeks later, participants in all four arms will once again be asked to complete the knowledge and behavioral expectation questionnaire. Figure 1 illustrates the trial design.

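### The matched t-test listed for the video's effect can only pair a post-video score with the 14-day score: it estimates net change, and neither shows the video's impact nor isolates decay of its effect

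*Protocol article*

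**What the plan says.** The Secondary outcomes paragraph under Statistical methods {20a} is meant to evaluate the "immediate and medium-term effects of the SAS video intervention on behavioral expectations to reduce sodium intake". It carries over the methods of the primary analysis and then gives an open list, introduced by "The methods include, but are not limited to", which contains the independent t-test, a "matched t-test for dependent groups" and a multilevel regression model. The next sentence states the data: "we will analyze the mean scores of the Sodium questionnaire at time points 0 and after 14 days". It puts the emphasis on what the video does to scores in the Intervention Arm.

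Trial design {8} fixes when scores exist. Intervention participants see the video and "thereafter be asked to complete a questionnaire to assess knowledge on dietary sodium and behavioral expectation". Two weeks later, "participants in all four arms will once again be asked to complete the knowledge and behavioral expectation questionnaire". In Table 1 the column headed 0 is allocation, and no questionnaire is marked there for any arm.

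Objectives {7} adds a hypothesis about knowledge: it should rise in the short and medium term, "but knowledge may decrease during the 2-week follow-up phase".

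**The concern.** A paired test is a natural way to show an effect when one score precedes the intervention and the other follows it. The reference to time point 0 invites that reading here, but the design has no such score. In the Intervention Arm both members of the pair follow the video.

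Two misreadings could follow. A change from the first to the second questionnaire could be reported as the video's impact when it reflects answering the same questions twice or looking things up in between. Conversely, a real loss of the video's effect could be hidden by a retest gain, or a general fall in scores could be blamed on the video wearing off. The protocol itself treats a question effect as plausible: Explanation for the choice of comparators {6b} sets up Exposed versus Un-exposed at time point 2 to study it.

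The score is also unclear. The paragraph concerns behavioral expectation but names the Sodium questionnaire.

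**Working it through.** **1. Which pairs exist (Trial design {8}, Table 1).**

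| Arm | Before video / time 0 | Time point 1 | Time point 2 |
|---|---|---|---|
| Intervention | none | score after sodium video | score |
| Do-nothing Exposed | none | score, no video | score |
| Attention Placebo | none | score after unrelated video | score |
| Do-nothing Un-exposed | none | none | score |

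The only possible pair is time point 1 with time point 2, in the first three arms.

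**2. What the contrasts estimate.** Let V be the immediate video effect, L the part of it lost over two weeks, and R the change from repeat questioning and outside learning, taken as equal across arms. With m the no-video mean at time point 1:

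- Intervention: m + V, then m + V − L + R. Paired change = R − L.
- Do-nothing Exposed: m, then m + R. Paired change = R.
- Difference in change = (R − L) − R = −L.
- Between-arm difference: V at time point 1, V − L at time point 2.

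V cancels from the paired change. The paired change equals −L only if R = 0. The difference in change removes R.

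**3. The plan's own figure.** Sample size {14} gives d = 0.1, one-sided 0.01 and 80% power: n = 2(2.326 + 0.842)²/0.1², about 2008 per arm, or 2009 with the t distribution. The stated 2009 reproduces. It belongs to the independent two-sample comparison; no figure is given for the matched test.

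**4. Illustrations.** Completers per arm: 2500 × 0.8 = 2000, using the protocol's 20% attrition. The protocol gives no correlation between the two scores and no retest shift, so the values below are assumptions (SD = 1, correlation 0.5 to 0.7).

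SE of paired change = √(2(1 − ρ)/2000).

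| V | L | R | Paired change (z) | Difference in change (z) |
|---|---|---|---|---|
| 0.5 | 0.2 | 0 | −0.20 (−8.9 to −11.5) | −0.20 (−6.3 to −8.2) |
| 0.5 | 0.2 | 0.1 | −0.10 (−4.5 to −5.8) | −0.20 (−6.3 to −8.2) |
| 0.5 | 0.2 | 0.2 | 0.00 (0) | −0.20 (−6.3 to −8.2) |
| 0 | 0 | 0.1 | +0.10 (4.5 to 5.8) | 0.00 (0) |

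The same loss of 0.2 SD appears as anything from −0.20 to 0.00. In the last row a video with no effect gives a clearly significant paired change.

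**5. Sensitivity to a small shift.** At ρ = 0.6, SE = √(0.8/2000) = 0.020. For a pure retest shift of 0.05 SD, the shift is 0.05/0.020 = 2.5 standard errors:

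- two-sided 0.05: 1 − Φ(1.96 − 2.5) = 71%;
- one-sided 0.01 in the direction of the shift: 1 − Φ(2.326 − 2.5) = 57%, moving from about 33% at ρ = 0.3 to 89% at ρ = 0.8.

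**6. Precision of the controlled contrast.** SE of the difference in change = 0.020 × √2 = 0.028 at ρ = 0.6. For a difference of 0.1 SD at one-sided 0.01, power is Φ(0.1/0.0283 − 2.326) = Φ(1.21), about 89%. At ρ = 0.5 the SE is 0.0316 and power is Φ(0.84), about 80%.

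**The case against.** The matched test is one entry in an open list. The text does not tie it to one arm, nor explicitly to time points 1 and 2, and the focus on the Intervention Arm stands in the following sentence. A reader might infer that an Intervention-only paired test is how the video will be judged. The documents do not support that: randomised between-arm t-tests are planned at both time points (Primary outcomes; Explanation for the choice of comparators {6b}), and the secondary analysis inherits them.

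A reader might also infer that the paired change measures nothing of use. That too goes too far. The hypothesis in Objectives {7} is worded as a possible fall in knowledge, and a post-video to 14-day change estimates exactly that net change. What it cannot do is attribute the change to the video's effect wearing off.

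In completers, the difference in change equals the time point 2 between-arm difference minus that at time point 1, and both are planned. A multilevel model is named as well, and its terms may be left to an analysis plan that is not shown. This stands, and it makes the fix cheap. But two separate t-tests do not themselves test the change.

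Finally, the 57% depends on an assumed correlation and on the direction of the test. A one-sided test for a decrease would almost never flag a retest gain. The one-sided 0.01 level is also the sample size setting, not one stated for this test.

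None of this supplies the missing pre-video score. The paragraph still names a paired test for the video's effect and a time point at which nothing is measured.

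**Conclusion.** The point holds as a limited fault in a stated method. The matched t-test cannot show the video's impact, because its only possible pair starts after the video and has no control. It does not isolate decay of the video's effect from repeat questioning or outside learning, but it does estimate net change. That the pair must be time point 1 with time point 2 is an inference from the schedule, and a firm one, since no other pair exists.

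The primary result and the planned between-arm estimates for both outcomes are not at risk. What is at risk is the interpretation of within-arm change. Its size cannot be fixed from the protocol. Under assumed retest gains of 0 to 0.2 SD, a loss of 0.2 SD would show as −0.20 to 0.00. The difference in change isolates the loss only if repeat questioning and outside learning act equally in the arms compared, and among completers.

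**What to change.** In the Secondary outcomes paragraph:

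1. Replace time point 0 with time point 1.
2. Name the score analysed: behavioral expectation here, and likewise knowledge for the hypothesis in Objectives {7}.
3. Report within-arm paired changes descriptively only.
4. Test change in the video's effect by the arm-by-time contrast in the multilevel model already planned: Intervention versus Do-nothing Exposed, with Attention Placebo as support. The Un-exposed arm has no time point 1 score and cannot enter this contrast; it keeps its role in the time point 2 comparisons.

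The change is to wording and to one model term. It needs no new data, arms or participants. The price is precision: the interval for a difference in change is √2, about 1.4, times as wide as that for a single-arm change when the arms have equal size and variance.
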